# Geriatric assessment and intervention in older vulnerable patients undergoing surgery for colorectal cancer: a protocol for a randomised controlled trial (GEPOC trial)

**DOI:** 10.1186/s12877-021-02045-9

**Published:** 2021-01-30

**Keywords:** Colorectal cancer, Comprehensive geriatric assessment, Surgery, Frailty, Sarcopenia, Exercise

## Abstract

**Background:**

The incidence of colorectal cancer (CRC) increases with age. Older patients are a heterogeneous group ranging from fit to frail with various comorbidities. Frail older patients with CRC are at increased risk of negative outcomes and functional decline after cancer surgery compared to younger and fit older patients. Maintenance of independence after treatment is rarely investigated in clinical trials despite older patients value it as high as survival. Comprehensive geriatric assessment (CGA) is an evaluation of an older persons’ medical, psychosocial, and functional capabilities to develop an overall plan for treatment and follow-up. The beneficial effect of CGA is well documented in the fields of medicine and orthopaedic surgery, but evidence is lacking in cancer surgery. We aim to investigate the effect of CGA on physical performance in older frail patients undergoing surgery for CRC.

**Methods:**

GEPOC is a single centre randomised controlled trial including older patients (≥65 years) undergoing surgical resection for primary CRC. Frail patients (≤14/17 points using the G8 screening tool) will be randomised 1:1 to geriatric intervention and exercise (*n* = 50) or standard of care along (*n* = 50) with their standard surgical procedure. Intervention includes preoperative CGA, perioperative geriatric in-ward review and postoperative follow-up. All patients in the intervention group will participate in a pre- and postoperative resistance exercise programme (twice/week, 2 + 12 weeks). Primary endpoint is change in 30-s chair stand test. Assessment of primary endpoint will be performed by physiotherapists blinded to patient allocation. Secondary endpoints: changes in health related quality of life, physical strength and capacity (handgrip strength, gait speed and 6 min walking test), patient perceived quality of recovery, complications to surgery, body composition (Dual-energy X-ray absorptiometry and bioelectric impedance), serum biomarkers, readmission, length of stay and survival.

**Discussion:**

This ongoing trial will provide valuable knowledge on whether preoperative CGA and postoperative geriatric follow-up and intervention including an exercise program can counteract physical decline and improve quality of life in frail CRC patients undergoing surgery.

**Trial registration:**

Prospectively registered at Clinicaltrials.gov NCT03719573 (October 2018).

**Supplementary Information:**

The online version contains supplementary material available at 10.1186/s12877-021-02045-9.

## Background

Colorectal cancer (CRC) is the third most common cancer worldwide accounting for 1.8 million new cases in 2018 [1]. The incidence of CRC increases with age [2], with a median age at time of diagnosis of 70 years in Denmark [3]. As the population is getting older, an increasing number of older patients with CRC is expected in the future [4, 5].

The mainstay in treatment of localised CRC is resection [6]. Implementation of better perioperative care, minimal invasive surgery and enhanced recovery pathways have made cancer surgery available for a larger proportion of patients with CRC [7]. Surgery itself and complications from surgery increase the risk of functional decline and loss of independence which can be difficult to regain [8]. The burden of treatment as well as possible treatment outcomes are strong determinants of older patients’ preferences [9]. Maintenance of independence and health related quality of life represent preferred treatment outcomes over standard oncological outcomes (e.g. disease free survival) for older patients [9–11]. In general, surgery is considered safe for older patients and the primary risk factor for poor surgical outcome, usually defined as surgical complications or survival, is not age but comorbidity [12], frailty [13, 14] and sarcopenia [15]. However, loss of independence is reported in 1 in 5 patients older than 65 years undergoing surgery for CRC [8, 16].

Frailty is recognised as an independent risk factor and has been described as “A medical syndrome with multiple causes and contributors that is characterized by diminished strength, endurance, and reduced physiologic function that increases an individual’s vulnerability for developing increased dependency and/or death” [17]. Frail patients are more susceptible to adverse effects from external stressors such as surgery [13]. Identifying frail people is therefore crucial for more careful planning of surgery and treatment. Merely screening for frailty brings awareness of patient comorbidity and capacity and is associated with reduced mortality after surgery [18]. Frailty is not a permanent state but potentially reversible [19] since some comorbidities are modifiable, as are both physical capacity and nutritional status.

Comprehensive Geriatric assessment (CGA) is hitherto the most appropriate way to examine the overall health situation of the older frail patient [20]. CGA is a multidomain and usually multidisciplinary work tool used for systematic assessment of an older person’s medical, psychosocial, as well as functional capabilities and limitations in order to develop an overall plan for interventions and follow-up [21]. CGA assesses known pathology and can uncover unrecognized health issues [22]. Furthermore, a prospective study has shown that CGA can assess the risk of postoperative complications in older patients undergoing elective CRC surgery [23]. Nonetheless, CGA is time consuming and may not be needed for all older patients. Several more rapid frailty screening tools have therefore been developed to identify which patients will benefit from a CGA [24]. The recommendations from the International Society for Geriatric Oncology (SIOG) from June 2014 [25] find the G8 questionnaire to be equally sensitive or superior when compared to other screening tools. For patients with an abnormal G8 score (≤ 14/17) a full CGA is recommended [26, 27].

One of the most important factors leading to frailty is low muscle strength, functional performance and low muscle mass (i.e. sarcopenia) [17]. Progressive resistance training is the single most effective intervention to increase muscle strength, muscle mass and functional performance in healthy older individuals [28] and in different patient populations [29–32]. Physical exercise is therefore recommended by WHO [33] and is shown to be safe and beneficial among older patients with cancer [34, 35].

Yet, there is a need for randomised controlled trials investigating the effect of the CGA in cancer surgery with patient-centred outcomes as preferred by the older patients. Thus, the aim of the present study is to evaluate the effect of pre-operative CGA and physical exercise, post-operative geriatric in-ward review and exercise, and post-operative geriatric rehabilitation on patients´ physical and functional performance.

## Methods/design

### Trial design

This is a randomised controlled trial (RCT) comparing a multidisciplinary intervention to standard of care in older frail patients with CRC undergoing curative intended surgery. The trial design follows the SPIRIT guidelines for randomised controlled trials. Trial design can be seen in Fig. 1.

**Fig. 1 Fig1:**
[figure not shown]
GEPOC trial design. Abbreviation: ERAS Enhanced Recovery After Surgery

### Participants

A total of 100 patients will be recruited from a single tertiary surgical centre at Herlev and Gentofte Hospital, Copenhagen University Hospital.

#### Inclusion criteria

For inclusion in the study, all the following must be fulfilled: (i) age ≥ 65 years; (ii) frailty evaluated with a G8 questionnaire score ≤ 14/17; (iii) scheduled for elective primary CRC surgical resection; and (iv) histologically proven adenocarcinoma.

#### Exclusion criteria

None of the following should apply if the patient is eligible for the study: (i) neoadjuvant treatment; (ii) severe physical disability that hinders training; and (iii) inability to give informed consent.

### Randomisation

Randomisation is performed electronically in REDcap randomisation module from permuted blocks and stratified for Eastern Cooperative Oncology Group (ECOG) performance status. Patients will be randomized 1:1 to an intervention group and a control group.

### Management in both groups

All patients will be evaluated at the multidisciplinary team (MDT) conference before surgery. Surgical resection is according to national guidelines [6] and follow the local Enhanced Recovery After Surgery (ERAS) programme with minimal invasive surgery [36]. The ERAS programme also includes pre-operative participation in the ERAS school where patients receive (i) education from a nurse specialist in preparation for surgery, (ii) education about nutrition from a dietician and (iii) education on mobilisation and lung physiotherapy from a physiotherapist. After surgery the ERAS programme includes early mobilisation and oral nutrition at the surgical ward. The geriatric intervention will not affect the surgical planning (e.g. laparoscopic or open surgery) nor the timing for surgery.

### Geriatric intervention

All patients in the intervention group will receive a three-phased intervention: pre-operative-, peri-operative- and post-operative. All phases consist of geriatric interventions including a physical exercise programme.

#### Geriatric assessment and tailored interventions

The pre-operative phase consists of a home visit with a CGA with tailored interventions on identified health issues. The contents of the geriatric assessment is based on recommendations from SIOG [37]. The following domains are assessed: comorbidity, medication, social status, cognition, psychological status, functional status and nutrition. Assessment tools and possible interventions can be seen in Supplement 1.

The peri-operative phase includes post-operative geriatric review in addition to surgical review in the surgical ward. This includes early detection and treatment of medical complications (e.g. delirium, infections, atrial fibrillation) and multidisciplinary issues (e.g. discharge planning, pain management, nutrition).

The post-operative phase: Geriatric follow-up on identified health problems if needed.

#### Exercise programme

All phases of the programme are supervised by experienced physiotherapists.

Pre- and post-operative phases: supervised group-based exercise programme scheduled twice a week from inclusion until surgery. After a two-week post-operative pause the programme continues for further 12 consecutive weeks. The exercise programme is a 1-h programme including 15 min warming up, 35 min of progressive resistance training followed by 10 min of cool down. The progressive resistance training focuses on large muscle groups and follows recommendations from American College of Sports Medicine [38–40]. The programme has previously been described by Mikkelsen et al. [41] The pre- and post-operative phases of exercise are both conducted in the Department of Physiotherapy and Occupational Therapy, Herlev Hospital.

Perioperative phase: patients will receive supervised training from physiotherapists throughout the stay when admitting on the surgical ward. The training programme is adapted to each individual in accordance with the surgical procedure (e.g. laparoscopic or laparotomic approach) and conferred with the surgical staff before each session. The exercise programme is conducted in the surgical ward. Details can be seen in Supplement 2. After discharge patients will be provided with an activity tracker. They will be guided in setting goals in relation to activity throughout the study.

### Endpoints and measurements

Baseline test prior to randomisation includes test of physical strength and capacity, questionnaire of quality of life and estimation of body composition. Study data are collected on the 2. and 14. postoperative day, and at the end of study 14 weeks after surgery (Fig. 2).

**Fig. 2 Fig2:**
[figure not shown]
SPIRIT flow diagram. Abbreviations: CGA Comprehensive Geriatric Assessment, ERAS Enhanced Recovery After Surgery, CAS Cumulated Ambulation Score, BI Bioelectric Impedance, DXA Whole-body dual-energy X-ray absorptiometry. * Physical tests: 30-s chair stand test, 6 + 10-m usual gait speed, handgrip strength, 5-times-sit-to-stand, six-minute-walk-test. ** questionnaires: European Organization for Research and Treatment of Cancer Quality of Life Questionnaire Core 30 (EORTC QLQ-C30) + Elderly Cancer Patients Module (EORTC QLQ-ELD14). *** Serum biomarkers: Interleukin-6, YKL-40, C-reactive Protein, Olink panel, Growth Differentiation Factor 11 + 14, Vitamin D

### Primary endpoint

The primary endpoint of the GEPOC study is change in 30-s Chair Stand Test (30s-CST) from baseline to 14 weeks after surgery. The 30s-CST measures a combination of muscle strength and endurance and is highly sensitive in older patients [42]. A high test-score is regarded as a predictor for functional independence in older patients [43–45] as it measures the ability to rise from a chair. The 30s-CST has also been used and tested in cancer patients [46, 47].

### Secondary endpoints

**Muscle strength and functional capacity**: changes in hand grip strength, 6 m and 10 m habitual gait speed, 5-times-sit-to-stand and 6-min-walk-test. The 5-times-sit-to-stand is performed separately in accordance with latest guidelines for sarcopenia [48]**.** Changes in the physical tests will be reported from baseline at two and 14 weeks after surgery and changes from 2 weeks after surgery at 14 weeks after surgery. Additional information regarding the tests are described in Supplement 3. Cumulated Ambulation Score (CAS) [49] will be measured in the postoperative period, as a measurement of day-to-day basic mobility. For acute abdominal surgery a poor CAS is associated with pulmonary complications and low activity in the first postoperative week [50] and CAS has been shown to be predictive for discharge to a higher level of dependence [49]. CAS will be compared between groups and investigated as a predictor for poor postoperative outcome independent of patient allocation to control or intervention group. All physical tests will be performed in the same sequence by a physiotherapist blinded to patients’ allocation to control or intervention group.**Patient reported outcome measures:** Patient’s perspective of recovery in the perioperative period will be assessed with Quality of Recovery-15 (QoR-15). QoR-15 is a patient reported outcome questionnaire that quantifies recovery from surgery and anaesthesia [51, 52].Health related Quality of Life (HRQoL) will be assessed with European Organization for Research and Treatment of Cancer Quality of Life Questionnaire Core 30 (EORTC QLQ-C30) conjoined with the module for older patients with cancer (QLQ-ELD14). The questionnaires incorporate functional scales, symptom scales and a global health and quality-of-life scale [53, 54].**Postoperative complications (30 + 90 days):** The occurrence of postoperative complication within 30 + 90 days after surgical resection of CRC will be graded from 0 to 5 based on the classification system validated by Clavien and Dindo [55]. Further details are described in Supplement 4.**Body composition and sarcopenia:** Whole-body dual-energy X-ray absorptiometry (DXA) scan (GE lunar iDXA, GE Healthcare Technologies, Madison, Wisconsin, U.S.) and bioelectrical impedance (BI) assessment (Body Composition Monitor, Fresenius Medical Care, Bad Homburg v.d.H., Germany) will be used to measure body composition. Sarcopenia will be reported according to the revised guidelines from the European Working Group on Sarcopenia in Older People [48].**Length of stay and readmission rate:** The postoperative length of stay defined from the day of surgical resection of CRC to the day of discharge from the surgical ward will be calculated. Readmission rate is defined as any unplanned hospitalisation within 30 and 90 days of discharge is registered.**Initiation and completion of adjuvant chemotherapy:** Patients will be treated with adjuvant chemotherapy according to national guidelines if indication for chemotherapy is found [56]. Type of chemotherapy, dose, number of series and adverse events are registered.**Survival and mortality:** Cancer- and treatment-related mortality or other cause of mortality will be registered throughout the study and a during a follow-up period of 5 years.**Serum biomarkers:** Blood samples will be taken 1–3 days before surgery, at the first and second postoperative day and at the end of study. Serum biomarkers will be analysed as part of cooperative research project REBECCA (“Biomarkers for patients with colorectal cancer - providing new information on diagnosis, treatment effect, side-effects and prognosis” (translated from Danish)). The REBECCA study is approved by the Regional Ethics Committee (H-2-2013-078) and the Danish Data Protection Agency (jr. nr. 2007-58-0015; HEH-2014-044; I-suite nr. 02771 and PACTIUS P-2019-614).

To investigate the influence of CGA and CGA-based exercise for older frail patients with CRC the following serum biomarkers will be measured: C-reactive protein (CRP), interleukin-6 (IL-6), YKL-40, Growth Differentiation Factor (GDF) 11 and 15, vitamin D and the Olink immune-oncology panel [57] (a panel of 92 serum proteins proteins associated with inflammation and immunology and cancer). Further details are given in Supplement 5.

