### Statistical analysis

#### Sample size

Calculation of statistical power is based on the estimated effect of CGA based interventions on physical performance. According to a previous study focusing on patients with osteoarthritis, the clinically relevant change in the 30s-CST was set at 2.6 repetitions [58]. Based on results from prior studies focusing on patients with advanced cancer, a standard deviation (SD) of around 3 has been reported in the 30s-CST [59, 60]. To be able to detect a difference of 2.6 repetitions in the between-group difference in the 30s-CST at the 12-week assessment and to obtain a type I error rate of 5% and a power of 90%, a sample size of 29 patients per study arm will be needed. To account for an expected dropout rate of ~ 40%, we decided to increase this number to a group size of 50. Thus, the aim will be to include a total of 100 patients in the study.

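### Length of stay stops when the patient leaves the surgical ward rather than the hospital, and the readmission window does not say which discharge starts it (minor, secondary endpoints only)

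*Protocol article*

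**What the plan says.** Length of stay and readmission are both secondary endpoints; the abstract (Methods) lists them among "serum biomarkers, readmission, length of stay and survival". Their definitions stand together in the protocol article under Secondary endpoints:

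- Length of stay: "The postoperative length of stay defined from the day of surgical resection of CRC to the day of discharge from the surgical ward".
- Readmission: "Readmission rate is defined as any unplanned hospitalisation within 30 and 90 days of discharge is registered". The sentence does not say whether this is discharge from the ward or from the hospital.
- Complications, in the same section, run from the operation: "The occurrence of postoperative complication within 30 + 90 days after surgical resection of CRC".

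Under Geriatric assessment and tailored interventions, the intervention arm receives geriatric review on the surgical ward in addition to the surgical review. It covers early detection and treatment of medical complications, and "multidisciplinary issues (e.g. discharge planning, pain management, nutrition" among other matters. Blinding is described for the physiotherapists who perform the physical tests. The article states no rule for transfers between wards.

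**The concern.** The definition names the surgical ward as the place whose discharge ends the stay. Taken at its word, a patient who moves to a medical or geriatric bed stops accruing stay that day, although still an inpatient. The days that follow belong to no endpoint.

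This matters for a comparison between arms because one component of the intervention acts on the surgical ward and on discharge itself. If it changes how often patients are moved, or how long they remain in hospital afterwards, ward-based stay will differ between arms for a reason unrelated to total time in hospital.

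The Discussion also cites earlier work on geriatric surgical services for reduced length of hospitalisation and length of stay. A figure limited to one ward does not bear cleanly on that comparison.

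The readmission sentence adds a smaller difficulty: for a transferred patient its starting point can be read in two ways, with different results.

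**Working it through.** **What the article gives.** It states no length of stay, transfer share, extra bed-days or readmission risk, so it has no figure of its own on this point to reproduce. Its sample size concerns the chair stand test ("the clinically relevant change in the 30s-CST was set at 2.6 repetitions", SD about 3, two-sided 5%, 90% power). A two-sample t-test calculation gives 28.97, so the stated 29 per arm is reproduced. That figure does not depend on the definitions discussed here. Everything below rests on assumed values.

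**1. Days lost from length of stay.** Let p be the share of patients transferred out of the surgical ward and e the mean further days in hospital. Then

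mean ward stay = mean hospital stay − p × e.

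| p | e = 3 days | e = 7 days | e = 14 days |
|---|---|---|---|
| 5% | 0.15 | 0.35 | 0.70 |
| 10% | 0.30 | 0.70 | 1.40 |
| 20% | 0.60 | 1.40 | 2.80 |

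Mean hospital stay is understated by 0.15 to 2.8 days over this range.

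**2. Effect on the comparison.** With I for intervention and C for control,

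ward difference (I − C) = hospital difference (I − C) − (p_I × e_I − p_C × e_C).

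- Equal products in both arms: the last term is 0 and the comparison is unbiased.
- 20% transferred in the intervention arm, 5% in control, 7 further days in each: 1.40 − 0.35 = 1.05 days, a spurious shortening under the intervention.
- The same shares reversed: 0.35 − 1.40 = −1.05 days, a spurious lengthening.

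The sign is open.

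**3. Which discharge starts the readmission window.** Take a transferred patient who stays 3–14 further days.

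- Ward discharge: the clock runs while the patient is still in hospital and cannot be readmitted. Of the 30 days, 30 − 3 = 27 down to 30 − 14 = 16 remain at risk; of the 90 days, 87 down to 76.
- Hospital discharge: the patient has the full 30 and 90 days, but the 3–14 days after transfer count in neither length of stay nor readmission.

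The two definitions fit together only if both use hospital discharge.

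**4. Should the readmission clock start at surgery instead?** Assume stays of 6 days (control) and 4 days (intervention).

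- Constant hazard giving 25% in 30 days: λ = −ln(0.75)/30 = 0.00959 per day. From discharge both arms have 30 days at risk: 25% and 25%. From surgery they have 24 and 26 days: 1 − exp(−24λ) = 20.6% and 1 − exp(−26λ) = 22.1%.
- Hazard falling with time since surgery (decay constant 10–40 days, scaled to 20.0% in control from discharge): from discharge, 20.0% against 20.9–23.9%, a gap of 0.9–3.9 points. From surgery, 17.4–19.2% against 19.1–23.3%, a gap of 1.7–4.1 points.

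A surgery-based clock does not remove the dependence on length of stay, and here it slightly enlarges it.

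**The case against.** The strongest reply is that the article is a condensed account. It never says that a transfer ends the stay; that is inferred from the words naming the ward. The full protocol, which is not shown, may deal with transfers and with deaths before discharge, and silence on such detail is no fault in an article. The direction is open too: review on the surgical ward that treats medical complications there could mean fewer transfers in the intervention arm, not more. This stands as a limit on what can be claimed. It does not remove the point, because the article states an end-point for the interval, and that end-point is the ward.

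A reader might go further in four ways that the documents do not support.

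- **That the intervention would look better than it is.** This needs more transfers, or longer stays after them, in the intervention arm. No figure supports it, and the bias could run the other way.
- **That deaths on the ward are scored as short stays.** The definition speaks of discharge and says nothing about death. Mortality is registered separately, and complications are graded 0 to 5.
- **That timing readmission from discharge is an error because complications run from surgery.** Only a discharged patient can be readmitted. A discharge-based clock gives everyone discharged alive equal time at risk, and step 4 shows that the alternative is no better.
- **That the 90-day readmission window is cut off for stays over 8 days.** The final assessment is "at the end of study 14 weeks after surgery", and 14 × 7 − 90 = 8. The inference assumes that readmissions stop being recorded at that visit. The article does not say so; it says hospitalisations within 90 days of discharge are registered, and it follows mortality for 5 years.

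**Conclusion.** The point holds as a minor one. The stated length-of-stay definition, read literally, leaves out hospital days after transfer from the surgical ward, and the readmission sentence does not say which discharge it means. Because only the intervention arm receives geriatric ward review with discharge planning, the omission could bias the length-of-stay comparison in either direction.

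The size cannot be known from the documents. The understatement of 0.15–2.8 days rests on assumed transfer shares of 5–20% and 3–14 further days. It becomes bias only to the extent that share times extra days differs between arms. The choice of discharge as the start of the readmission window is sound. Two secondary endpoints are affected; the primary endpoint and the sample size are not.

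**What to change.** Reword the two definitions and add one summary:

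1. Length of stay: from the day of resection to discharge from hospital, counting days in any ward after transfer.
2. Readmission: keep the 30- and 90-day windows counted from discharge, and state that this is the same hospital discharge that ends length of stay.
3. Report days alive and out of hospital to day 90 after surgery as a supporting summary. Its window is the same for every operated patient; it counts transferred days and readmission days, and it handles in-hospital death without a separate rule.

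If the full protocol already has a transfer rule, the article's wording need only be aligned with it.

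The cost is wording and the use of existing hospital records. At the time of the article 36 of the planned 100 patients had been included, and admission and discharge dates for them should be recoverable. The downside is that hospital stay will be somewhat more variable than ward stay and less comparable with surgical-ward audits. Ward stay can still be tabulated beside it.
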